# Multicentre open label randomised controlled trial of immediate enhanced ambulatory ECG monitoring versus standard monitoring in acute unexplained syncope patients: the ASPIRED study

**DOI:** 10.1136/bmjopen-2022-069530

**Published:** 2023-02-23

**Keywords:** ACCIDENT & EMERGENCY MEDICINE, Adult cardiology, Pacing & electrophysiology, GENERAL MEDICINE (see Internal Medicine), Cardiology

## Abstract

**Introduction:**

Diagnosing underlying arrhythmia in emergency department (ED) syncope patients is difficult. There is a evidence that diagnostic yield for detecting underlying arrhythmia is highest when cardiac monitoring devices are applied early, ideally at the index visit. This strategy has the potential to change current syncope management from low diagnostic yield Holter to higher yield ambulatory monitoring, reduce episodes of syncope, reduce risk of recurrence and its potential serious consequences, reduce hospital admissions, reduce overall health costs and increase quality of life by allowing earlier diagnosis, treatment and exclusion of clinically important arrhythmias.

**Methods and analyses:**

This is a UK open prospective parallel group multicentre randomised controlled trial of an immediate 14-day ambulatory patch heart monitor vs standard care in 2234 patients presenting acutely with unexplained syncope. Our patient focused primary endpoint will be number of episodes of syncope at 1 year. Health economic evaluation will estimate the incremental cost per syncope episode avoided and quality-adjusted life year gained.

**Ethics and dissemination:**

Informed consent for participation will be sought. The ASPIRED trial received a favourable ethical opinion from South East Scotland Research Ethics Committee 01 (21/SS/0073). Results will be disseminated via scientific publication, lay summary and visual abstract.

**Trial registration number:**

ISRCTN 10278811.

STRENGTHS AND LIMITATIONS OF THIS STUDYThe ASPIRED trial uses non-blinded randomisation to compare immediate enhanced ambulatory ECG monitoring versus standard monitoring in acute unexplained syncope patients.The primary outcome measure is a patient focussed measure very relevant to the population of patients who suffer syncope.We are using health economic analysis and a separate embedded qualitative study to assess the wider implications of using immediate enhanced ambulatory ECG monitoring in this population.In contrast to the few published studies on ambulatory monitoring in syncope patients which are generally single centred, without any comparative group and with heterogeneous patient populations and device capabilities, this study is multicentred and includes a standard care group.

## Introduction

### Background and rationale

Syncope (or blackout) is common; 650 000 patients present to UK emergency departments (EDs) every year. The three underlying causes are neurocardiogenic (including simple faint), postural hypotension (blood pressure fall on standing) and cardiac disease (structural heart disease or cardiac arrhythmia). Diagnosis is difficult and is not made in around 50% of patients after assessment.^1–4^ While vasovagal and postural syncope are relatively benign, serious pathology (affecting 7 out of every 100 patients at 1 month after ED attendance^5^) include arrhythmia (an abnormal heart rhythm). When cardiac arrhythmias are detected, they are most commonly asystolic pauses, reflex bradycardia or advanced atrioventricular block, with tachycardia being the minority.^6^

The difficulty in the ED is to differentiate between the causes of syncope and identify patients at higher risk. This can be complicated as many patients have fully recovered on ED arrival and their examination and presenting ECG may both be normal. The current method for establishing cardiac arrhythmia as the cause of syncope rests on correlating the arrhythmia with symptoms. The lack of efficacy and availability of commonly used monitoring devices means most high and medium risk patients are admitted to the hospital for observation and telemetry (if available), with escalating costs.^1^ Unfortunately, many (around 50% of patients after assessment) still end up being discharged without a diagnosis.^7^

In general, syncope reoccurs in around 50% of patients within a year. Recurring episodes increase hospital admissions, health costs and importantly reduce the quality of life of patients. While there is a wide variation in the literature with respect to the number of syncope episodes and recurrence rates pretreatment and post-treatment^6 8–10^ once a cardiac arrhythmia diagnosis is made and treatment initiated, around only 10% of patients will have a 1-year recurrence^11^ and syncope episodes will drop by over 90%.^11^

There is evidence that the diagnostic yield for detecting underlying arrhythmia is highest when cardiac monitoring devices are applied early after syncope, ideally at the index visit^1–3^. To solve the problems with current routine ECG monitoring devices, several novel ambulatory devices have recently been developed^1 12–15^. These devices are non-invasive, water-resistant, have no leads or wires, are discreet to wear and are CE-marked for clinical use in the UK. They continuously monitor the heart for up to 14 days including during sleep, in the shower and during moderate exercise and some have a button for patients to capture symptomatic events. They offer medium duration high fidelity ECG recording and are well tolerated^16 17^. At the end of the monitoring period, patients return the devices back to the company (by email) or NHS (to be downloaded) for analysis. The PATCH-ED pilot study helped establish trial methods and number of available participants informing this randomised controlled trial (RCT)^1^. This pilot study showed a novel ECG monitoring device was able to detect serious cardiac arrhythmia requiring treatment in a significant proportion of patients and demonstrated the potential to influence clinical management decisions relating to hospital admission and participant outcomes.

The ASPIRED RCT will compare a novel ambulatory cardiac monitoring device with standard practice in syncope patients. We hypothesise that applying cardiac monitoring early after syncope at the index visit is the optimum strategy to detect, diagnose, treat and exclude underlying cardiac arrhythmia.

### Study objectives

#### Primary

To determine whether immediate, enhanced (14 days) ambulatory ECG monitoring decreases the number of self-reported episodes of syncope at 1 year compared with standard care monitoring in acute unexplained syncope patients.

#### Secondary

To determine whether immediate, enhanced (14 days) ambulatory ECG monitoring in acute unexplained syncope patients can:

Decrease the number of episodes of self-reported syncope at 90 days, and 2 years compared with standard care monitoring.Decrease the time to detection of clinically significant cardiac arrhythmia compared with standard care monitoring.Increase the rate of detection of clinically significant cardiac arrhythmia at 90 days and 1 year compared with standard care monitoring.Increase the rate of ECG/symptom correlation at 90 days and 1 year compared with standard care monitoring.Demonstrate cost-effectiveness compared with standard care monitoring.Decrease the number of episodes of syncope identified in the medical records at 90 days, 1 and 2 years compared with standard care monitoring.Decrease the index hospital admission rate and duration of hospital stay compared with standard care monitoring.Decrease 90 days, 1-year and 2-year syncope recurrence rates (identified in the medical records and self-reported) compared with standard care monitoring.Increase patient satisfaction compared with standard care monitoring.Decrease the rate of 30 day, 1-year and 2-year all-cause death compared with standard care monitoring.In the intervention group, by reporting the timing of detection of clinically significant cardiac arrhythmia what is the optimum duration of acute ambulatory ECG monitoring.Increase the affect rate of diagnostic testing and therapeutic intervention.

## Methods and analysis

### Study design

This is a UK open prospective parallel group multicentre RCT of an immediate 14-day ambulatory patch heart monitor versus standard care monitoring in 2234 participants presenting acutely with unexplained syncope. The patient focused primary endpoint will be number of episodes of syncope at 1 year (table 1).

**Table 1 T1:** Study summary in PICO format

P: Population	Adults presenting acutely to UK hospitals with syncope remaining unexplained after initial ED/AMU assessment
I: Intervention	14-day ambulatory heart monitor placed on patients
C: Comparator	Standard care monitoring
O: Primary Outcome	Number of self-reported episodes of syncope at 1 year

AMU, acute medicine unit; ED, emergency department.

#### Study eligibility

Two thousand two hundred and thirty-four adult (16 years or older) participants presenting acutely to UK hospitals with syncope remaining unexplained after initial ED or acute medicine unit (AMU) assessment will be enrolled. Syncope will be defined as transient loss of consciousness (TLOC) with inability to maintain postural tone and immediate complete spontaneous recovery without medical intervention^18^.

##### Inclusion criteria

Syncope remains unexplained after initial ED/AMU assessment.Aged ≥16 years.Patient has capacity.Local resident (ie, resident within local health board so will not be lost to medical record follow-up).<5 self-reported episodes of syncope in the previous month.

##### Exclusion criteria

Obvious underlying cause after assessment.Features of vasovagal syncope (see box 1) AND absence of structural heart disease AND normal physical examination AND normal ECG.Arrhythmia on prehospital or hospital ECG as likely cause of syncope.Postural hypotension (symptomatic postural drop >20 mm Hg AND suggestive history).Confirmed diagnosis of pulmonary embolus or acute myocardial infarction.Radiological diagnosis or clinical signs/symptoms of cerebrovascular accident/transient ischaemic attack or subarachnoid haemorrhage.Evidence of:Haemorrhage.Alcohol or illicit drugs.Epileptic seizure.Hypoglycaemia.Head trauma.Other obvious cause of syncope as presumptive cause of TLOC.Inability to consent.Previous recruitment into the study.Patient in custody or prison.Aged<16 years.Patient does not reside within local health board and will therefore be lost to medical record follow-up.Five or more self-reported episodes of syncope in previous 4 weeks.

Pregnancy is not an exclusion criteria.

Box 1Features of vasovagal/postural syncopeAssociated with typical symptoms of reflex syncope (eg, light-headedness, feeling of warmth, nausea, vomiting).After sudden unexpected unpleasant sight, sound, smell or pain.In association with micturition, defaecation, cough, laughter, venepuncture, blood phobia.After prolonged standing or crowded, hot places.During a meal or after eating a meal.With head rotation or pressure on carotid sinus (eg, tumour, shaving, tight collars).Associated with standing up quickly from a sitting or lying position.Long history (years) of recurrent syncope with low-risk features with the same characteristics of the current episode.

#### Participant recruitment

Recruitment will take place in around 30–40 NHS acute tertiary and district hospitals. Figure 1 summarises the study design and participant recruitment.

**Figure 1 F1:**
[figure not shown]
Schematic diagram of the study design and participant recruitment. AMU, acute medicine unit; ED, emergency department; GP, general practitioner.

### Randomisation and interventions

Randomisation will be performed using a web-based randomisation service to ensure allocation concealment, managed by Edinburgh Clinical Trials Unit (ECTU). The allocation sequence will be created by an ECTU database programmer using computer-generated pseudo-random numbers. Participants will be randomised, 1:1, between the two study arms. Stratification by site will be used to ensure there will not be a significant imbalance between the number randomised to intervention and control at any site. Stratification by other site-level characteristics will not be performed.

Standard care will include all care usually given to unexplained syncope patients at each participating site along with some form of standard care monitoring such as but not limited to wired inpatient telemetry, Holter style monitoring or implantable ECG recorder. The study will be conducted over 4 years. Recruitment will take place over 18 months. Intervention group participants will be fitted with a 14-day ambulatory heart monitor. All participants will be followed up for 2 years after index event.

#### Outcome measures

##### Primary endpoint

Number of self-reported episodes of syncope at 1 year.

##### Secondary endpoints

Within trial cost-effectiveness (cost per syncope avoided and cost per quality-adjusted life year (QALY) gained), and lifetime cost per QALY gained at (a) 1 year and (b) 2 years.Number of self-reported episodes of syncope at (a) 90 days and (b) 2 years, those identified in the medical records at (c) 90 days, (d) 1 year and (e) 2 years, and syncope recurrence rate at (f) 90 days, (g) 1 year and (h) 2 years.Index presentation hospital (a) admission rate and (b) duration of hospital stay.Patient satisfaction (measured using a patient questionnaire) at 1 year.Clinically significant cardiac arrhythmia (serious and/or symptomatic cardiac arrhythmia, box 2) at (a) 90 days, (b) 1 year and (c) 2 years.(a) 30-day, (b) 1-year and (c) 2-year all-cause death.Detection of diagnostic ECG/symptom correlation (symptomatic) at (a) 90 days, (b) 1 year and (c) 2 years.Time to detect clinically significant cardiac arrhythmia (ie, time to clinician being aware).In the intervention group, duration of enhanced ambulatory ECG monitoring required to detect clinically significant cardiac arrhythmia.Number and type of diagnostic tests and therapeutic interventions at (a) 1 year and (b) 2 years.

Box 2Definitions of clinically significant cardiac arrhythmiasVentricular fibrillation.^*^Ventricular tachycardia (VT) ≥120 beats per minute (bpm) for ≥30s.^*^VT ≥120 bpm for <30 s (≥4 beats).^*^Complete or 3rd degree heart block.^*^Second degree atrioventricular heart block Mobitz type II.^*^Second degree atrioventricular heart block Mobitz type I.Pause ≥6 s.^*^Sinus pause ≥2.5 s when awake or ≥4 s at night (but <6 s).Sinus bradycardia <30 bpm.^*^Bradycardia <40 bpm for ≥30 s.^*^Bradycardia <40 bpm for <30 s.Sick sinus syndrome with alternating sinus bradycardia and tachycardia.Junctional/idioventricular rhythm ≥30 s in duration.Supraventricular tachycardia >100 bpm ≥30 s in duration.Atrial flutter/fibrillation with ventricular rate >100 bpm or <60 bpm ≥30 s in duration.New atrial flutter/fibrillation ≥30 s in duration.All arrhythmias will also be classed as symptomatic or asymptomatic during monitoring period.*‘Serious’ clinically significant cardiac arrhythmia.

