### Trial assessments

#### Participant identification

Potential participants will be identified from EDs/AMUs or other acute settings and approached either during their ED/AMU or hospital stay or contacted after discharge and invited to take part in the study.

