#### Participant consent

Potential participants will be given a Participant Information Sheet (PIS). Potential participants will be randomised within 72 hours of their hospital attendance. If a patient has been discharged from the hospital, then they will be contacted by the local clinical team or research team (if part of the clinical team), and a copy of the PIS will be emailed or posted out to the patient. The PIS will also be available on the trial website. A delegated member of the local study team will seek verbal consent over the telephone and will sign the consent form on behalf of the participant. The original consent form will be filed in the Investigator Site File and a copy will be sent to the participant. Alternatively, the patient can attend the hospital with travel expenses, to provide written informed consent in person. The ambulatory ECG device can be sent to the participant’s address or collected from the local study team if randomised to the intervention arm. Each participating centre will upload screening information of non-identifiable potentially eligible patients who were approached to participate in the study, onto the study database. Participants are free to withdraw from the study at any point or can be withdrawn by the investigator.

Participants will have an electronic case report form completed at randomisation (table 2). Recruited participants regardless of allocation group, will be referred for syncope assessment as per local service protocol and subsequent investigations will be arranged at the discretion of the treating clinician. Participants randomised to the intervention arm will be fitted with a 14-day ambulatory heart monitor (Preventice BodyGuardian Mini) applied by the study team as soon after randomisation as possible. The ambulatory ECG monitor will be placed on the participant’s chest wall over the sternum, connected directly to an ECG electrode sticker (figure 2). The participant’s skin does not require shaving but is cleaned prior to attaching the device, which are easily removed by the participant after 14 days. The monitor can be worn by both women and men.

**Table 2 T2:** Study assessments

Assessment	Screening	Day 1 baseline	Monthly	90 days	Every 3 months	1 year	2 years
**Window of time for evaluation**	**n/a**	**n/a**	**±14 days**	**±14 days**	**n/a**	**±30 days**	**±30 days**
Assessment of eligibility criteria	X						
Informed consent	X						

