**Figure 2 F2:**
[figure not shown]
14-day ambulatory heart monitor (Preventice BodyGuardian Mini).

Participants will be required to press the button on the heart monitor after any syncopal event. They will also record symptomatic episodes in a paper diary. The participant will wear the ambulatory ECG monitor for a maximum of 14 days after which they will remove and return it in a prepaid envelope to Preventice UK. The monitor will be reported by a cardiac physiologist, shared with the participant’s local study team, placed in the participant’s health record and shared with the participant’s treating clinician. Treatment of device findings will be at the discretion of the treating clinician at each site. The participant’s general practitioner (GP) will be informed that the participant has been enrolled in the study and will be informed of the results of any ECG investigations via routine hospital clinical correspondence. Participants will be informed of the results of any ECG investigations via routine hospital clinical correspondence. Any study participant with a serious arrhythmia (box 2) on the ECG report will be contacted as soon as possible by the local team and managed appropriately according to local policy.

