All participants will be contacted on a 4-weekly basis ±14 days for 2 years via automated text message or email (whichever they prefer) with a link to a brief web-based questionnaire asking for the number of syncope events experienced since their last response and how many of these they attended hospital for. Those who are unable to access digital forms of communication will receive phone calls. They will also be asked since their last response how many times they have visited their GP practice for any reason including all face-to-face, telephone and online consultations. This will import directly into the central ECTU study database. This patient-reported data will be used to inform the primary endpoint. The small number of participants unable to access digital forms of communication and participants not responding for 3 consecutive months will receive a phone call from the central study team (blinded to participant’s study arm allocation) to collect missing data, ensure no syncope episodes have occurred and to encourage continued future engagement. Participants with a mean of 5 or more episodes/month will also receive a phone call from the central study team to ensure that participants are recording true syncope events and are seeking appropriate medical advice.

We were very thoughtful about the potential impact of COVID-19 when designing this study including ensuring ambulatory ECG monitors can be sent directly to patients and designing participant follow-up to ensure no additional research related hospital visits are required.

Participants will also be contacted at one and 2 years±30 days, by the central study team (blinded to participants study arm allocation) to complete a quality-of-life questionnaire. In the event of non-response, participants will be contacted on up to three occasions. The participants’ involvement in the study will cease at 2 years. Endpoint data including NHS resource usage will be extracted by the local study team from routine hospital electronic healthcare records at 90 days, 1 and 2 years and will be entered into a bespoke database. ECTU will collect and clean primary data and perform primary and secondary analyses.

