#### Data analysis plan

The primary outcome, number of self-reported episodes of syncope in the 12 months following randomisation, will be analysed by negative binomial regression. The primary outcome event rate ratio (14-day ambulatory heart monitor vs standard care) will be reported with its 95% CI. An offset term for follow-up duration will be included to account for participants with partial follow-up.

The secondary outcomes for the number of syncope episodes at 90 days and 2 years, will be analysed similarly. Binary secondary outcomes will be analysed by logistic regression, reporting the OR (14-day ambulatory heart monitor vs standard care) and its 95% CI. Full details of analysis, including the estimand(s) of interest and methods for handling missing data, will be written into a Statistical Analysis Plan, which will be finalised prior to database lock without knowledge of the unblinded treatment allocations.

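### Index admission and length of stay are outcomes to be reduced, but for patients randomised as inpatients or after discharge they are wholly or partly settled before allocation

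*Protocol article*

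**What the plan says.** Three parts of the protocol article bear on this.

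- **Outcome.** The secondary objectives include: "Decrease the index hospital admission rate and duration of hospital stay compared with standard care monitoring". The Secondary endpoints section carries this through as "Index presentation hospital (a) admission rate and (b) duration of hospital stay". Both are tied to the index presentation, not to the time of randomisation.
- **Timing of entry.** Under Participant identification, patients are "approached either during their ED/AMU or hospital stay or contacted after discharge and invited to take part in the study". Under Participant consent: "Potential participants will be randomised within 72 hours of their hospital attendance". The same section sets out a route for people who have gone home: "If a patient has been discharged from the hospital, then they will be contacted by the local clinical team or research team". Consent can then be taken by telephone. The text after Figure 2 shows that supplying the device outside hospital was part of the design: "ensuring ambulatory ECG monitors can be sent directly to patients".
- **Analysis.** The Data analysis plan says: "Binary secondary outcomes will be analysed by logistic regression". It does not limit the admission endpoint to patients whose disposition was still open, and it does not say that stay is counted from randomisation. It leaves estimands to a Statistical Analysis Plan that is not shown.

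**The concern.** An outcome can respond to allocation only if it is still open at allocation. Index admission is a single decision early in the episode, and the article plans for some participants to be randomised after it. For them, admission is a baseline characteristic that has been listed as an outcome. The same is true of the whole stay for those already home, and of the days already spent for those still in hospital.

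Fewer hospital admissions is one of the benefits claimed in the Abstract, and the Introduction says the pilot showed potential to influence admission decisions. If the comparison includes many participants whose admission was already settled, a result near zero has two explanations: the monitor does not change admissions, or most participants entered too late for it to do so. The comparison as worded cannot tell these apart. Hospitalisation is also a resource item in the Cost-effectiveness analysis section. Any bed-days before randomisation that are counted there add noise and no information on the intervention.

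**Working it through.** **Step 1: what is still open at randomisation**

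| Status at randomisation | Index admission | Index length of stay |
|---|---|---|
| Before the admit/discharge decision | Open | Open |
| Inpatient | Fixed (yes) | Days so far fixed, remainder open |
| Discharged | Fixed | Fixed |

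Allocation can alter admission only in the first row. It can alter stay in the first row and in part of the second.

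**Step 2: inputs**

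From the Sample size section: 1117 participants per arm. That section concerns the primary outcome, and the article states no power or effect for index admission, so there is no stated figure to reproduce for this endpoint. The following are not in the article and are assumptions:

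- f, the share already admitted or discharged at randomisation: 0 to 80%
- d, the reduction in admission among those still undecided: 10 points (5 points as a check)
- p0, the admission rate under standard care: 50% (30% and 70% as checks)

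**Step 3: dilution of the admission effect**

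The true difference is zero in the share f and d in the share 1-f, so the difference among all randomised is f × 0 + (1-f) × d = (1-f)d. With d = 10 points:

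- f = 25%: 0.75 × 10 = 7.5 points
- f = 50%: 0.50 × 10 = 5 points
- f = 80%: 0.20 × 10 = 2 points

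**Step 4: effect on power**

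Two-sided 5% test of two proportions, n = 1117 per arm, p1 = p0 - (1-f)d, p̄ = (p0 + p1)/2:

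power = Φ{[(1-f)d - 1.96 √(2p̄(1-p̄)/n)] / √([p0(1-p0) + p1(1-p1)]/n)}

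For p0 = 50%, d = 10 points and f = 50%, p1 = 45% and p̄ = 47.5%. The numerator is 0.05 - 1.96 × 0.02113 = 0.0086 and the denominator is 0.0211. The ratio is 0.41, so power is 66%.

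| f | Difference seen | Power, all randomised |
|---|---|---|
| 0 | 10 points | 99.7% |
| 25% | 7.5 points | 94.5% |
| 50% | 5 points | 65.8% |
| 75% | 2.5 points | 21.8% |

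Across p0 of 30%, 50% and 70%, power is 66% to 75% at f = 50% and 22% to 26% at f = 75%. If d is 5 points, power is 66% to 75% at f = 0 and 22% to 26% at f = 50%.

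**Step 5: what restriction recovers**

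Among undecided participants the difference is d and the sample is (1-f)n per arm. With similar variance, the ratio of test statistics (restricted to all randomised) is

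[d √((1-f)n)] / [(1-f)d √n] = 1/√(1-f),

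which is 1.15, 1.41 and 2.24 at f = 25%, 50% and 80%. The smaller sample costs less than the dilution does.

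**Step 6: limits of the arithmetic**

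Steps 3 to 5 apply to admission as a yes/no outcome. They do not carry over to length of stay, because inpatients can still show an effect on the remainder. No size is derived for stay or for cost.

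**The case against.** The strongest objection is that the article is a condensed protocol. It names the endpoint in one line, gives no analysis set for it, and leaves estimands to a Statistical Analysis Plan. The full case report form is not shown either, so disposition at randomisation may already be collected. This stands in part: nothing here shows that the data are lacking, and an analysis plan could restrict the set. But the objective and endpoint are already fixed on the index presentation, next to an entry route that runs past discharge. Deferring estimands does not resolve that mismatch.

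A second objection is that comparing all randomised participants is valid for the strategy as delivered within 72 hours, and that restriction answers a different question in a selected group. This also stands in part, and is why the full comparison should be kept as supportive. It does not help a reader to interpret a null result.

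Three stronger readings are tempting and are not supported:

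- **That the comparison is biased between arms.** Randomisation balances whatever was settled beforehand. The consequence is dilution and noise.
- **That length of stay is fixed for everyone randomised late.** Inpatients still have a remaining stay that allocation could change.
- **That the trial will report no reduction in admissions.** The article gives no value for f. Under the assumptions above (50% control rate, 10 points), power is still 94.5% at f = 25% and about 66% at f = 50%. A missed effect becomes likely only at higher f or with a smaller effect.

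**Conclusion.** The point holds as a mismatch between the endpoint and the timing of randomisation. Index admission is settled before allocation for anyone randomised as an inpatient or after discharge. Index stay is wholly settled for the discharged and partly settled for inpatients. An admission effect is multiplied by 1-f. That factor follows from the entry rules alone. The point differences and power figures rest on assumed values of f, d and the control admission rate, so the actual size in this trial is unknown. It might be small if most participants are randomised before the decision, and large if few are.

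The effect on cost is noise only, unquantified, and arises only if bed-days before randomisation are counted, which the article does not say. The primary outcome and its sample size are not touched. This is worth correcting because the change is cheap and a null result on admissions would otherwise be hard to interpret, but it concerns one secondary endpoint.

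**What to change.** Reword the endpoint and its analysis as follows:

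1. Use disposition at randomisation (undecided, inpatient, discharged) as a baseline variable, and report the share in each category by arm.
2. Make the main analysis of index admission the participants randomised before the admit/discharge decision. Keep the comparison of all randomised participants as supportive. Because disposition is known before allocation, the restriction preserves the randomised comparison.
3. Define length of stay as time from randomisation to discharge, in participants still in hospital at randomisation.
4. Count hospital days from randomisation in the incremental cost.

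The cost is a change of wording in the endpoint and the analysis plan, plus times of randomisation, admission decision and discharge. Recruitment and sample size do not change. The downside is a smaller and more selected analysis set for this endpoint: at f = 50% the admission analysis would hold about 0.5 × 1117 ≈ 558 participants per arm, and its result would apply to patients enrolled before the decision rather than to everyone in the trial.
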